#### Economic evaluation

The incremental cost-utility ratio (ICUR) will be calculated by subtracting the costs of the CG from the costs of the IG and dividing the result by the QALYs for the CG subtracted from the QALYs for the IG. The incremental costs and the incremental utility will be modeled by generalized linear models, taking into account the distribution of both costs and effects.

To estimate the uncertainty related to the ICUR, we will calculate 95% confidence intervals for the mean cost differences using the non-parametric confidence interval. Bootstrapping with 1000 replications will be performed.

Bootstrapped cost effects pairs will be plotted on cost-effectiveness planes and used to estimate cost-utility acceptability curves (CUACs). In the cost-utility planes, the ‘x’ axis represents the difference in QALYs and the ‘y’ axis the difference in costs. CUACs demonstrate the probability that an intervention is cost effective at a specific ceiling ratio, which is the amount of money society is willing to pay to gain one extra unit of effect. Willingness to pay values will range from 0€ to 50,000€ [26].

The robustness of the estimates will be addressed by conducting sensitivity analyses. This analysis will comprise a variation in the unit cost of the primary care medical or nurse visits, in the costs of the workshop leaders’ hourly wage and in the venue rental cost.

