#### Quantitative quasi-experimental design

The study population will consist of adults aged 65 years or older residing in the disadvantaged neighborhoods of Barcelona (Spain) selected for the study. The intervention neighborhoods (*n* = 2) and comparison neighborhoods (n = 2) will be selected on a convenience basis, ensuring similar socioeconomic characteristics, including the percentage of people with primary studies or less, unemployment rates and disposable household income rates.

The intervention will be offered to adults aged 65 years or older, living in one of the two selected neighborhoods, and recruited through primary care centers, social services and civic centers for older people. Once individuals have accepted to participate, there will be a pre-registration process that will record their names and telephone numbers. Later, the participants will be contacted by telephone to arrange an appointment, in which the person will be informed individually about the study. After agreement, he/she will sign the informed consent form and complete a questionnaire.

To calculate the sample size, we took into account that 45% of people aged 65 years or more in Barcelona reports fair or poor health [21] and assumed that the intervention would reduce this prevalence by 17 points. Accepting an alpha risk of 0.05% and a power of 80% in a unilateral contrast, and assuming a loss of 10%, we estimated that a theoretical sample of 79 participants in the IG and 79 participants in the CG will be needed.

We expect to recruit 80 individuals in the IG and 80 in the CG. To have similar groups, the recruitment settings (primary care centers, social services and civic centers) would be taken into account, by selecting the same percentage of people from each setting.

The exclusion criteria are the following:Participants with difficulties in maintaining participation for 6 months.Participants with difficulties in understanding or expressing themselves in Spanish or Catalan.

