#### Quantitative quasi-experimental design

##### Main outcomes

Social support will be measured through questions taken from the Medical Outcomes Study: Measures of Quality of Life Core Survey (MOS) [22] and NSHAP questionnaires [20]. Psychological morbidity will be measured through Goldberg’s General Health Questionnaire (GHQ-12) [23], and health-related quality of life will be measured through the EuroQoL (EQ-5D) questionnaire [24]. Objective information will be obtained on visits to the primary care center during the year before and after the intervention through access to the electronic records of the primary care centers.

All these variables will be measured simultaneously in individuals in the IG and CG. Data will be collected through baseline and post-intervention questionnaires administered by trained researchers.

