#### Economic evaluation

The economic evaluation will be conducted from a health system (primary care) perspective, including direct costs of the program and the primary care health services used. The time frame will be 6 months and consequently no discounting will be applied to the calculations.

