##### Effects

The effects of the intervention will be measured in quality adjusted life years (QALY), through the EQ-5D questionnaire. Spanish tariffs will be used to estimate the utility of health states described by the participants. QALYs [25] will be assessed at baseline and at 6 months (end of the intervention), and QALYs will be calculated by multiplying utility by the amount of time a patient spent in a particular health state. Linear interpolation will be used for transitions between health states. QALYs will be assessed at baseline and at 6, 12 and 18 months.

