#### Quantitative quasi-experimental design

A descriptive analysis will be conducted to rule out significant differences between baseline characteristics (sociodemographic variables and outcomes studied) in the IG and the CG. The chi-square test will be used to compare qualitative variables. Continuous variables with normal distribution will be compared using the Student t test, and the Mann-Whitney U test will be used in non-normally distributed variables. In case of differences, a further multivariate effectiveness analysis will be conducted adjusting for these variables.

Further descriptive analyses will be conducted for results at baseline and at follow-up. Categorical outcomes will be described through percentages, and continuous outcomes will be described through mean scores and standard deviations or the median and interquartile range, as required. Differences between pre- and post-intervention measurements will be assessed and compared using the McNemar test, paired t-test, or sign test, according to the type of variable and distribution.

To assess the effectiveness of the intervention, a two-sample McNemar test will first be conducted to analyze differences in changes in pre- and post-intervention results between the IG and the CG for each main outcome. In those outcomes showing differences between the groups at the baseline measurement, Poisson regression models with robust variance will be built. In each model, the independent variables will be the group (IG or CG), the pre-intervention measurements for the outcome assessed and any relevant characteristics that differ between the groups at the baseline assessment.

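### The economic analysis specifies no adjustment for baseline EQ-5D utility or prior-year visits, so a systematic baseline gap between the non-randomised groups would pass straight into the ICUR

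*Protocol article*

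**What the plan says.** All references are to the protocol article.

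- **Data analysis, Economic evaluation.** The ICUR is the cost difference between the groups, obtained by "dividing the result by the QALYs for the CG subtracted from the QALYs for the IG". On modelling, the section says: "The incremental costs and the incremental utility will be modeled by generalized linear models, taking into account the distribution of both costs and effects". No covariate is named. The sensitivity analyses vary the unit cost of visits, the workshop leaders' wage and the venue cost.
- **Outcome measures, Effects.** QALYs come from EQ-5D utilities: "Linear interpolation will be used for transitions between health states". The economic section sets the horizon: "The time frame will be 6 months and consequently no discounting will be applied to the calculations".
- **Study setting, Quantitative quasi-experimental design.** The two intervention and two comparison neighbourhoods "will be selected on a convenience basis, ensuring similar socioeconomic characteristics". The same percentage of people is to come from each recruitment setting in both groups.
- **Data analysis, Quantitative quasi-experimental design.** For outcomes that differ at baseline, regression models are to include "the pre-intervention measurements for the outcome assessed and any relevant characteristics that differ between the groups at the baseline assessment".
- **Main outcomes.** Records will supply "visits to the primary care center during the year before and after the intervention", so prior use of primary care is available for each person.

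**The concern.** The economic evaluation uses the same non-randomised groups as the effectiveness analysis and is open to the same confounding. The effectiveness analysis has at least a conditional safeguard against baseline differences. The economic analysis states none: the ICUR is written as a direct subtraction, the models are justified by distribution alone, and no sensitivity analysis looks at imbalance.

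QALYs are especially exposed, because an area-under-the-curve QALY contains the baseline utility itself. If one group starts in better health, it collects more QALYs whether or not the programme works. A systematic difference of this kind would carry through to the ICUR, the bootstrapped cost-effectiveness plane and the acceptability curve. Cost-effectiveness is one of the stated hypotheses and one of the three specific objectives, so this result matters to the study's conclusions.

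**Working it through.** The document states no QALY, cost or ICUR figure, so there is nothing of its own to reproduce.

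**Inputs from the document:** a 6-month horizon (T = 0.5 year); linear interpolation between baseline and 6 months; 80 people per group, or 72 after the assumed 10% loss. (The Effects section also mentions QALYs at 12 and 18 months; the 6-month frame is used here.)

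**Assumed inputs, not in the document:** true utility effect at 6 months e = 0.03 to 0.08; baseline gap d up to 0.05; persistence of the gap to 6 months r = 0.5 to 1.0; utility SD 0.15 to 0.30; incremental cost 200 euros; 30 to 60 euros per visit.

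**Step 1. Weight of baseline utility.** QALY = T × (U0 + U6)/2 = 0.25 × (U0 + U6). With gap d (intervention minus comparison), the unadjusted incremental QALY is 0.25 × (d + r·d + e). The effect contributes 0.25·e and the imbalance 0.25·d·(1 + r).

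**Step 2. Gap that reverses the sign.** A gap against the intervention group reverses the sign once it exceeds e/(1 + r):

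| e | r = 0.5 | r = 0.7 | r = 1.0 |
|---|---|---|---|
| 0.03 | 0.020 | 0.018 | 0.015 |
| 0.05 | 0.033 | 0.029 | 0.025 |
| 0.08 | 0.053 | 0.047 | 0.040 |

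**Step 3. Illustration at e = 0.05, r = 0.7.** The true gain is 0.25 × 0.05 = 0.0125 QALY.

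- No gap: 200/0.0125 = 16,000 euros per QALY.
- Gap +0.05: 0.25 × (0.05 + 0.035 + 0.05) = 0.03375 QALY; 200/0.03375 = about 5,900 euros per QALY.
- Gap −0.05: 0.25 × (−0.05 − 0.035 + 0.05) = −0.00875 QALY, so the intervention appears dominated.

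The ICUR scales in proportion to the assumed cost; the sign of the QALY difference does not depend on it.

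**Step 4. Costs.** An imbalance of one visit per person moves the ICUR by 30/0.0125 = 2,400 to 60/0.0125 = 4,800 euros per QALY. Under these assumptions this is smaller than the utility part.

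**Step 5. Would the conditional rule suffice if borrowed?** The standard error of the baseline difference is SD × √(2/80), or 0.024 to 0.047 for SD 0.15 to 0.30. A two-sided 5% test then detects a true gap of 0.05 with power of only 56% down to 18%. Adjusting only after a significant difference would often miss a gap large enough to matter.

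**Step 6. What adjustment does.** In 4,000 simulated studies (72 per group, SD 0.25, r = 0.7, e = 0.05), the unadjusted difference averaged −0.009 QALY with a gap of −0.05 and +0.034 with +0.05. Regressing QALY on group and baseline utility gave 0.0125 and 0.0124, and the sampling SD fell from 0.019 to about 0.0075.

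**Step 7. Limit of the adjustment.** If a gap of 0.05 persists fully (r = 1) while the within-group slope of follow-up on baseline utility is 0.7, the residual bias is 0.25 × 0.05 × (1 − 0.7) = 0.00375 QALY. Without adjustment it is 0.25 × 0.05 × 2 = 0.025.

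**The case against.** The strongest reply is that the article does not commit to an unadjusted comparison. Generalised linear models can carry covariates. One with only a group term reproduces the two group means, so naming such models may hint that covariates were intended. The subtraction formula is the ordinary definition of an ICUR and fits adjusted increments equally well. Covariate lists are also often left to a fuller plan. A reader might infer that raw QALYs and costs will be compared; the text does not say so. What it supports is that no adjustment is specified. That remains a fault because the article sets out the estimator, the purpose of the models and the sensitivity analyses, and writes baseline adjustment for the effectiveness outcomes only.

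The article also shows that imbalance was considered. Neighbourhoods are matched on education, unemployment and income, and recruitment settings are balanced. The baseline comparison covers the outcomes studied, which include EQ-5D and visits. Strengths and limitations promises adjusted models where sociodemographic differences are found. It is therefore unsupported to say that the groups will differ; they may. But that promise concerns the quantitative part and sociodemographic variables, is conditional on finding a difference, and is not extended to the ICUR.

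Finally, a chance gap is sampling error, not bias, and the bootstrap would reflect it. This stands. Only a systematic gap biases the result, and the document gives no evidence of its size. A chance gap costs precision, which baseline adjustment also recovers.

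**Conclusion.** The point holds as a gap in specification with a real consequence. As written, the economic analysis names no adjustment for baseline utility or prior-year visits in a non-randomised comparison, and the QALY construction gives baseline utility the same weight as follow-up utility. That much follows from the text and simple algebra.

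The size is conditional. At an assumed utility effect of 0.05, a systematic gap against the intervention group above 0.025 to 0.033 reverses the sign of the incremental QALY; across effects of 0.03 to 0.08 the threshold runs from 0.015 to 0.053. The ICUR figures are illustrations resting on assumed effect, gap, persistence and cost. They should not be read as a forecast that the ICUR will be reversed. The plan should be changed; if a fuller analysis plan already names these covariates, the economic section need only say so.

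**What to change.** In the economic part of Data analysis, state that:

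- the QALY model includes group, baseline EQ-5D utility, age, sex, marital status, cohabitation status and educational level. Residential neighbourhood, also listed among the sociodemographic variables, must be left out because it is aliased with group;
- the cost model includes group, prior-year primary care visits or their cost, and the same sociodemographic covariates;
- these covariates enter regardless of any baseline significance test;
- both models are fitted within each of the 1000 bootstrap replicates, so that the ICUR, the plane and the acceptability curve all use adjusted increments;
- the unadjusted ICUR is reported as a sensitivity analysis.

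The cost is some wording and a little more code, since baseline EQ-5D, prior-year visits and the sociodemographic variables are already to be collected. The adjustment reduces bias but may not remove it fully if a systematic gap persists more strongly than the within-group slope implies; the report should say so.

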### Ethics considerations

Participants will be informed both verbally and in writing about the aims, methods, procedures and measures performed during the study. They will be also informed about ethics issues such as confidentiality, their right to ask any questions during the study, and their right to withdraw at any time without penalty. To ensure that all participants have received proper information about the study and have agreed to participate, all participants will be asked to sign a written consent form. The research team is committed to performing this study in accordance with the Good Clinical Practice Guidelines of the Declaration of Helsinki. This protocol was approved by the *Comité Ético de Investigación Clínica Parc de Salut Mar (code* n° 2015/6500/I).

## Discussion

### Strengths and limitations

A potential limitation of the study is the length of follow-up, since the post-intervention measurements will be carried out immediately after the end of the intervention (6 months). Therefore, we will not be able to assess its long-term effects. Another limitation of the quantitative part of the study is that, because the design is quasi-experimental, there may be some differences between the IG and the CG. However, a statistical comparison of the main sociodemographic variables will be assessed and if any differences are found, they will be taken into account in the adjusted regression models.

A strength of the study is that, as far as we know, it is the first to assess the effectiveness and cost-effectiveness of an intervention focused on reducing social isolation in older people in deprived neighborhoods in an urban environment. Importantly, this is a multi-approach evaluation assessing the process, effectiveness and cost-effectiveness of an intervention while using mixed methods (quantitative and qualitative). Furthermore, the tests applied to measure the main outcomes (social support, psychological morbidity and health-related quality of life) are validated tests that not only allow for assessment of the potential impact of the intervention but also for comparison with other studies.

### Implications

Aging is one of the greatest social and economic challenges for European societies. At the same time as cities are growing, their share of older residents is increasing. By 2025, more than 20% of European citizens will be 65 years or older [27]. Ensuring the integration of older people in society is essential to promote the wellbeing of older urban residents. Therefore, studies assessing the effectiveness and efficiency of potential interventions to reduce the social isolation of older people are urgently needed.

The results of this study will help to fill the knowledge gap in this area and might be especially useful for the development of social and public health policies and programs for older people in disadvantaged neighborhoods of urban areas.

## Abbreviations

CG: Comparison group
CUAC: Cost-utility acceptability curves
EQ-5: EuroQoL-5D
GHQ-12: Goldberg’s General Health Questionnaire
IG: Intervention group
ICUR: Incremental Cost-Utility Ratio
MOS: Measures of Quality of Life Core Survey
NSHAP: National Social Life, Health, and Aging Project
QALY: Quality Adjusted Life Years
